# Protocol for a randomized controlled trial exploring the brain mechanism and therapeutic effect of electroacupuncture on cognitive function and sleep quality in chronic insomnia

**DOI:** 10.1186/s12906-023-04242-y

**Published:** 2023-11-08

**Keywords:** Electroacupuncture, Chronic insomnia, Clinical trial, Randomized controlled trial, Brain mechanism

## Abstract

**Background:**

Insomnia is a prevalent sleep disorder that affects up to 15% of the population worldwide and is the second most common mental health issue. There is increasing interest in the effects of long-term insomnia on cognitive function. Electroacupuncture can effectively improve cognitive function and sleep quality, yet the underlying brain network mechanisms remain unclear. This study aims to explore the network regulatory mechanisms associated with enhanced cognitive function and sleep quality, providing theoretical support for the use of electroacupuncture in the clinical treatment of chronic insomnia.

**Methods:**

This study is divided into two parts. Sixteen individuals with chronic insomnia and 16 healthy controls of similar age and gender will be recruited in Study 1 to examine the brain network topology of individuals with chronic insomnia. Study 2 will be a randomized controlled trial with 120 chronic insomnia patients divided into three groups: Group A (electroacupuncture plus placebo drug), Group B (drug plus placebo electroacupuncture), and Group C (placebo electroacupuncture plus placebo drug). Participants will be exposed to 24 treatments over an 8-week period (3 times per week) and monitored for 12 additional weeks. The primary outcome measure will be changes in brainwave data from before to after the treatment. In addition, the Wisconsin Card Sorting Test and the Pittsburgh Sleep Quality Index will be utilized as secondary outcomes to measure from before to after treatment and during the follow-up. A correlation analysis will be conducted to explore links among modifications in brainwave patterns, Wisconsin Card Sorting Test scores, and Pittsburgh Sleep Quality Index scores. Additionally, any adverse events will be strictly monitored.

**Discussion:**

Electroacupuncture may represent an alternative treatment for chronic insomnia, and this trial is expected to reveal the brain mechanism by which electroacupuncture improves cognitive function and sleep quality in chronic insomnia patients.

**Trial registration:**

ChiCTR2200060150 (Chinese Clinical Trial Registry, http://www.chictr.org.cn, registered on 20 May 2022).

## Background

In modern society, individuals experience more stress, leading to higher prevalence rates of physical and mental illness. Chronic insomnia is one of the leading mental health issues worldwide, with a global prevalence rate of 10–15% [1, 2]. This disorder has considerable negative effects on the physical and mental well-being of those affected. It significantly impairs cognitive functioning, such as attention, memory, and alertness, leading to decreased learning capacity, reduced work productivity, and an increased risk of traffic accidents [3–5]. Elucidating cognitive changes in those with chronic insomnia is a crucial focus of clinical therapy.

Brain imaging studies have indicated that chronic insomnia patients exhibit changes in brain structure and function [6, 7]. Voxel-based morphometry analysis has revealed a decrease in gray matter volume in the dorsolateral prefrontal cortex of these patients [8]. Furthermore, studies have indicated changes in the functional connectivity between the frontal and parietal lobes in individuals with insomnia. There is a notable correlation between the functional connectivity between the left dorsolateral prefrontal cortex and the left inferior parietal lobule and scores on the self-report sleep quality questionnaire [9]. Experiments on sleep durations and sleep deprivation have revealed that the frontal lobe is more sensitive to these impacts, with abnormal activation occurring in the frontal lobe (such as in the DLPFC and MPFC) during cognitive-related tasks [10]. The dorsolateral prefrontal cortex is therefore a brain region commonly administered noninvasive stimulation to treat insomnia [11]. These findings suggest a connection between insomnia and abnormal frontal lobe function.

Acupuncture has been demonstrated to improve the sleep quality and cognitive functioning of those with insomnia [12–14]. Our previous studies also revealed that acupuncture can effectively enhance sleep quality in patients with insomnia and depression [15]. Nevertheless, the precise brain mechanisms of acupuncture have yet to be elucidated. We conducted a study on four individuals with insomnia to explore the immediate effects of acupuncture. The results showed that the functional network topology of the entire brain changed throughout the course of acupuncture, with a trend toward higher global and local efficiency than those of sham acupuncture. Notably, local efficiency in the dorsolateral prefrontal cortex was increased. Improving cognitive functioning and sleep quality may be linked to the restoration of brain network topology in patients with insomnia, and the dorsolateral prefrontal cortex may be a critical network node.

Graph theory analysis of brain networks has the advantage of allowing simultaneous analysis of the functional connectivity patterns among all brain areas, and it can also be used to investigate the organization of brain networks in response to various interventions, which may reveal the brain mechanism by which acupuncture intervention alleviates chronic insomnia. By using EEG, source localization and graph theory-based brain network analysis methods, this study aims to investigate the effectiveness of acupuncture in insomnia. It will help understand reveal the changes in brain network characteristics in patients with chronic insomnias, evaluate network changes after acupuncture treatment, and explore the correlation between these changes and improved cognitive function and sleep quality. This research has the potential to provide a theoretical basis for treating chronic insomnia in clinical practice, thereby improving the quality of life of this population.

## Methods

### Trial design and setting

The study is composed of two parts. Study 1 will recruit 16 individuals with chronic insomnia and 16 corresponding healthy controls, comparing changes in brain network topological characteristics between the two groups. Study 2 will be a randomized, double-blind controlled trial comprising 8 weeks of treatment and up to 12 weeks of follow-up. The experimental procedure is shown in Fig. 1.

This protocol was developed accordance with the Standard Protocol Items: Recommendations for Interventional Trials [16].

**Fig. 1 Fig1:**
[figure not shown]
Flow chart of the trial procedure

### Patient and public involvement

No patients have been involved.

### Patients

Participants with chronic insomnia will be recruited through posters (produced by the Publicity Department of the First Affiliated Hospital of Guangdong Pharmaceutical University), WeChat, and official WeChat accounts. The researchers will use the American Psychiatric Association DSM-5 criteria for insomnia to assign a diagnosis. Individuals who meet the inclusion criteria will receive free complimentary clinical testing and treatment to encourage enrollment. Before random allocation into groups, written informed consent will be obtained from eligible patients.

### Inclusion criteria

#### Study 1

The eligibility criteria for participants with chronic insomnia in Study 1 will be as follows: meet the diagnostic criteria for insomnia (depressive disorder due to another medical condition) as outlined in the DSM-5, have not received any systematic treatment for insomnia within the three months prior to the study, have a PSQI score of 8 points or higher, have a HAMD score of less than 7 points, and have a HAMA score of less than 14 points. Additionally, individuals must have had insomnia for at least 3 months, be between the ages of 18 and 50 years, be right-handed, and provide voluntary consent to participate in the study. Individuals between the ages of 18 and 50 years who have no sleep problems, have a PSQI score of 8 or less, have a HAMD score of 7 or less, have a HAMA score of 14 or less, have undergone a physical exam, are right-handed and have consented to participate in the study by signing the informed consent form will be considered eligible healthy controls.

#### Study 2

The inclusion criteria for patients with chronic insomnia in Study 2 will be the same as those in Study 1.

### Exclusion criteria

The exclusion criteria will be as follows: (1) severe mental illnesses such as depression, anxiety, or schizophrenia; (2) suicidal tendencies; (3) other severe systemic diseases that require treatment; (4) sleep apnea; or (5) a history of head trauma. In Study 2, in addition to the above exclusion criteria, subjects who are afraid of acupuncture and those with skin lesions at the puncture site will also be excluded.

### Randomization and blinding

The “Proc plan” feature of SAS 9.3(SAS Institute Inc., Cary, NC, USA) will be employed to create the necessary random allocation plan for the study. Eligible subjects will be assigned to Group A (electroacupuncture plus placebo drug), Group B (drug plus placebo electroacupuncture), or Group C (placebo electroacupuncture plus placebo drug) at a ratio of 1:1:1. All patients will be seen by appointment. During the acupuncture intervention, which will be completed in a quiet, separate treatment room to avoid contact and communication between patients in different groups, the therapist will instruct the patient to close their eyes. Only the acupuncturist performing the needle insertion throughout the trial will be aware of the patient’s group allocation. The subjects, evaluators of therapeutic effects, and individuals conducting the statistical analysts will be blinded to group allocation.

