### Electroacupuncture

The research team has previously demonstrated the effectiveness of acupuncture of the bilateral LU7 and KI6, DU20 and EX-HN3 in treating insomnia; thus, these acupoints will be the primary sites selected in this study, and their locations will be identified according to the WHO standard acupuncture locations [17].

The patient will lie down in a supine position. After the skin is disinfected, sterile adhesive pads will be affixed to the acupoints. Needles at LU7 and KI6 will be inserted to a depth of 0.3–0.5 inches. Needles at DU20 and EX-HN3 will be inserted at an angle of 30 degrees toward the back of the head and the tip of the nose, respectively, at a depth of 0.5 inches. The needles should be carefully lifted, inserted, and rotated three times until the patient feels achiness, heaviness, and numbness (known as de qi) at all acupoints. After 30 min, the needles will be removed.

Electroacupuncture will be administered using a sparse-dense wave with a frequency of 10/50 Hz and a current intensity of 0.5-1.0 mA, adjusted according to the patient’s tolerance.

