### Sham electroacupuncture

Participants in the control group will receive a sham acupuncture treatment at the same acupoints. After disinfecting the skin, adhesive pads will be placed on the acupoints, and placebo needles will be placed into the pads without penetrating the skin. The same procedures and treatment parameters as used in the acupuncture group will be followed. The patient will be informed that a mild electric current is being administered, although they may not feel it.

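### As written, the acupuncturist knows group A, B or C, although B and C get the same sham needling and a real/sham code would suffice

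*Protocol article*

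**What the plan says.** All references are to the protocol article.

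- Trial design and setting gives the label: "Study 2 will be a randomized, double-blind controlled trial".
- Randomization and blinding assigns patients to Group A (real electroacupuncture with placebo tablets), "Group B (drug plus placebo electroacupuncture), or Group C (placebo electroacupuncture plus placebo drug) at a ratio of 1:1:1". It then says "Only the acupuncturist performing the needle insertion throughout the trial will be aware of" the patient's group, and adds: "The subjects, evaluators of therapeutic effects, and individuals conducting the statistical analysts will be blinded to group allocation".
- Sham electroacupuncture describes one sham procedure, with no distinction between B and C: "placebo needles will be placed into the pads without penetrating the skin". It says that sham follows the procedures and settings of the real treatment. On sensation it says: "The patient will be informed that a mild electric current is being administered, although they may not feel it".
- Electroacupuncture describes needle manipulation until a needling sensation is felt and a current "adjusted according to the patient’s tolerance". It does not say what Group A patients are told about feeling the current.
- Placebo drug describes a starch tablet that looks like the active drug and is taken in the same way for the same period.
- The limitations paragraph of the Discussion accepts that needling cannot be done blind. It offers practitioner training, including a uniform way of communicating with patients, as mitigation.

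**The concern.** The design is a double dummy: every patient gets needling (real or sham) and a tablet (active or placebo). The operator must know which needling to deliver, but that does not require knowing which tablet the patient takes. By naming the three-way allocation as what the acupuncturist knows, the plan gives away the drug assignment within the two sham arms without any need.

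The acupuncturist has more scheduled contact with patients than anyone else in the trial. The PSQI rests on the patient's own report, is collected at weeks 0, 4, 8 and 20, and is the outcome on which the Sample size section rests. An operator who knows that one sham patient has an active hypnotic and another has starch may, without meaning to, convey different expectations. Blinding the evaluators and analysts does not remove that influence, because it acts on the patient before the questionnaire is completed. Performance on the Wisconsin Card Sorting Test could also respond to encouragement.

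B versus C is the one comparison in which the operator could be blind as well as the patient and the assessor. It also helps a reader judge whether the trial can detect an active treatment at all.

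**Working it through.** **Inputs**

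- Groups, ratio and who knows the allocation: Randomization and blinding.
- Sessions: 3 per week for 8 weeks (Intervention).
- 32 per group before dropout, 20% dropout, 120 in total (Sample size).
- Needling and tablet content: Electroacupuncture, Sham electroacupuncture, Drug and Placebo drug.

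**Step 1. The plan's own group size.** The figure of 32 reproduces as a superiority-by-a-margin t test with unequal variances. The inputs are a difference of 13.9 − 9.8 = 4.1, a margin of 1.5 (so 2.6 to detect), SDs of 3.1 and 3.2, and one-sided alpha 0.025. Power is 0.901 at 32 per group and 0.892 at 31. Then 32 / (1 − 0.20) = 40 per group, and 3 × 40 = 120. The present point uses only these counts, not the power calculation.

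**Step 2. What the operator needs to know.**

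| Group | Needling | Tablet | Code needed to needle |
|---|---|---|---|
| A | real | placebo | real |
| B | sham | active | sham |
| C | sham | placebo | sham |

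The third column never changes what the operator does. A two-value code is enough. It necessarily identifies Group A, because A is the only arm with real needling. Within sham it leaves B and C indistinguishable: 40 of the 80 sham patients, one half, have the active tablet. The reason given in the Discussion, that needling cannot be done blind, covers A against B and C. It does not cover B against C.

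**Step 3. Extent of the exposure.**

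- Patients: 2 × 40 = 80 of 120, or two thirds.
- Sessions per patient: 3 × 8 = 24.
- Planned sessions: 80 × 24 = 1,920 of 120 × 24 = 2,880.
- If the 20% assumed to drop out attended no sessions at all: 2 × 32 × 24 = 1,536 of 3 × 32 × 24 = 2,304, again two thirds.

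These figures count contacts in which the operator could have been blind to the drug. They do not measure bias.

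**Step 4. Can the bias be sized?** No. The document gives no drug-versus-placebo effect on PSQI and no estimate of expectation bias. Its only pair of means, 9.8 and 13.9, compares electroacupuncture with sham, so the difference of 4.1 is not a yardstick for B versus C.

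**Step 5. The sensation message.** Set side by side, the sham section tells the patient that the current may go unnoticed, and the electroacupuncture section is silent on what is said. That leaves open whether Group A hears the same words. It does not show that they hear different ones.

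**The case against.** **The sentence may mean only real versus sham.** Elsewhere the article uses the word group in a two-way sense: the sham section contrasts a control group with an acupuncture group, and the Sample size section speaks of EA and SA groups. No release of an A/B/C list or a drug code to the operator is described. This is a fair reading of a condensed sentence. But A, B and C are defined just before it in the same section, and the literal sense is the three-way allocation. If the intention was real/sham only, the sentence should say so.

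**The consequence is limited.** Patients, evaluators and analysts are stated to be blinded, the tablets are matched, and the acupuncturist is not described as an outcome assessor. The Outcomes section makes EEG primary and PSQI secondary. The Sample size section names PSQI as primary, which is a separate conflict. No section names B versus C as a powered comparison. All of this stands and keeps the point modest.

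**Stronger readings that the document does not support.**

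- A reader might infer that blinding as a whole is lost. It is not: operator knowledge of real versus sham is unavoidable and acknowledged, and the other parties remain blinded as stated.
- A reader might infer that sham patients can identify their arm because the intensity-adjustment step is missing. The sham section says that sham follows the procedures and settings of the real treatment, so that step may well be carried over.
- A reader might infer that the sensation message reveals the allocation. That is an argument from silence about Group A. The Discussion mentions uniform communication, the full protocol may hold a common script, and each patient hears only one version. The message also presents lack of sensation as compatible with real current, which can protect blinding.
- A reader might express an assumed bias as a share of the 4.1-point difference. That difference belongs to electroacupuncture versus sham, so the percentage would say nothing about B versus C.

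**Conclusion.** The point holds in a narrow form. Read literally, the plan discloses drug versus placebo to the acupuncturist for the 80 patients in the sham arms, over as many as 1,920 of 2,880 sessions, with no operational need. The avoidable loss is confined to the B versus C distinction. It is a possible route for expectation bias in a patient-reported outcome, not a demonstrated bias, and its size cannot be derived from the document.

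This rests on three assumptions: that the group allocation known to the acupuncturist is the A/B/C assignment, that B and C receive the single sham procedure described, and that sessions are delivered as planned. If the operator in practice receives only a real/sham code, the defect is one of wording.

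The sensation wording is a secondary risk to patient blinding and not a shown loss. The point is worth acting on because the remedy costs almost nothing; it does not put the trial's validity in doubt.

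**What to change.** - **Randomization and blinding:** state that the acupuncturist receives only a real or sham needling code, never A, B or C. State that the drug code is held elsewhere and that tablets are dispensed by kit number.
- **Electroacupuncture and Sham electroacupuncture:** state that the same wording about sensation is used in all three groups.
- **Optional:** ask patients at the existing week-8 visit which treatment they think they received, and report the answers by group. The absence of this question from an article is not an error.

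The cost is a relabelled allocation list and one common script, plus one form question if the optional item is adopted. No visit, sample size or treatment changes. Recruitment was scheduled to run from September 2022 to the end of December 2024, so the change helps only sessions not yet delivered. For sessions already delivered, the trial report should say what the acupuncturist actually knew.

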### Intervention

The treatment in this project will be administered by a professional acupuncturist with more than 3 years of experience. Treatment will be administered three times a week, with a minimum of 24 h between each session, over 8 weeks (24 treatment sessions).

An SDZ-V type Hua Tuo brand electronic acupuncture treatment instrument and needles (0.30 × 25 mm) will be used in this trial. Both the needles and the electroacupuncture device will be purchased from Suzhou Medical Supplies Factory Co., Ltd. (Production Enterprise License: Su Shi Yao Jian Xie Chan Xu 2001-0020; Registration Certificate Number: Su Shi Yao Jian Xie (Zhun) Zi 2004 No. 2,270,202).

### Electroacupuncture

The research team has previously demonstrated the effectiveness of acupuncture of the bilateral LU7 and KI6, DU20 and EX-HN3 in treating insomnia; thus, these acupoints will be the primary sites selected in this study, and their locations will be identified according to the WHO standard acupuncture locations [17].

The patient will lie down in a supine position. After the skin is disinfected, sterile adhesive pads will be affixed to the acupoints. Needles at LU7 and KI6 will be inserted to a depth of 0.3–0.5 inches. Needles at DU20 and EX-HN3 will be inserted at an angle of 30 degrees toward the back of the head and the tip of the nose, respectively, at a depth of 0.5 inches. The needles should be carefully lifted, inserted, and rotated three times until the patient feels achiness, heaviness, and numbness (known as de qi) at all acupoints. After 30 min, the needles will be removed.

Electroacupuncture will be administered using a sparse-dense wave with a frequency of 10/50 Hz and a current intensity of 0.5-1.0 mA, adjusted according to the patient’s tolerance.

### Sham electroacupuncture

Participants in the control group will receive a sham acupuncture treatment at the same acupoints. After disinfecting the skin, adhesive pads will be placed on the acupoints, and placebo needles will be placed into the pads without penetrating the skin. The same procedures and treatment parameters as used in the acupuncture group will be followed. The patient will be informed that a mild electric current is being administered, although they may not feel it.

### Drug

For a continuous treatment period of 8 weeks, 10 mg of zopiclone hydrochloride tablets will be taken orally before bedtime every day. The drug registration number is H20090001, the import permit number for psychotropic drugs is TPI20090302 and the approval number for imported drug packaging is National Drug Approval J20090050.

### Placebo drug

A placebo drug composed of starch will be administered with the same appearance, administration method, and treatment duration as the positive control drug.

### Follow-up

To evaluate the sustainability of the effects, a follow-up assessment will be conducted in the 20th week after the completion of baseline data collection.

